#### 4. Postoperatively two months after surgery

Neurological examination, CMS-survey, speech and language recording or bedside assessment and any medications given to treat CMS since last registration.

#### 5. Postoperatively twelve months after surgery

Neurological examination, speech and language status including speech and language recording or bedside assessment, medications given since last registration to treat CMS, chemo- and/or radiotherapy, neuropsychological assessment(s) if performed, final neuropathological classification of tumour, and additional neuroimaging performed since the first follow-up. Copies of the neuroimaging and descriptions performed pre- and postoperatively will be collected for central review.

### Acute and repeated neurosurgery

In case of emergency surgery (e.g. due to risk of incarceration or coma) information about the study and invitation to participate can be given within seven days postoperatively. These patients will be included in all parts of the study except for the recording and analysis of preoperative speech and language status.

In cases with repeat tumour surgery during the twelve months follow-up, the patient can re-enter the study and start a new follow-up programme (Fig. 1, Repeated Surgeries). A new pre-operative registration is then performed corresponding to the re-operation. Post-operative registrations will be performed again, and used in the analysis of risk related to first versus further surgeries. If surgery is performed again after the twelve months follow-up period, the patient will be re-invited to participate in the study.

**Fig. 1 Fig1:**
[figure not shown]
The follow up process in case of repeated surgeries

### Statistical considerations

In accordance with our surgical hypothesis of 50% risk reduction by less traumatic techniques, and assuming that 35% of the patients are operated using an approach with a low risk of CMS (assumed to be 10%) and the remaining 65% of patients are operated using other approaches (assumed carrying a 20% risk), a total of 450 patients have to be included to identify a 5% significance level and 80% power. Based on a projected overall risk of CMS of 20%, an estimated frequency of a specific SNP of 30%, and a projected doubled risk of CMS with this particular SNP, we will need to include a total of 343 patients to identify such a genetic predisposition at a 5% significance level with 90% power.

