#### Genetics

We will analyse the role of host genome variants on development, severity and recovery from CMS by carrying out broad genetic pathway profiling of all study participants using both non-CMS cases from the study cohort and non-CNS tumour patients as controls. Genotyping will use single nucleotide polymorphism (SNP) exome enriched arrays (e.g. Illumina Omni2.5-exome platform). We will apply agnostic genome-wide association studies (GWAS) as well as more complex pathway analyses. Thus, we will interrogate combined effects of multiple SNPs acting in the same pathways or protein-protein interaction complexes using our validated non-linear machine learning algorithm (artificial neural networks approach) [53, 54], which allows testing of a large range of pathways from various databases. This approach will yield hypotheses easier to test across cohorts and also provide mechanistic insights. We hypothesize that host genome variants explain at least 50% of the variation in incidence of CMS and at least 40% of the variation in severity, duration and level of recovery from the CMS.

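### The 343-patient, 90%-power statement fits one pre-chosen SNP that is never named; it does not apply to the agnostic GWAS and pathway testing that the protocol describes

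*Protocol article*

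**What the plan says.** Under Statistical considerations, the genetic calculation rests on three inputs: "Based on a projected overall risk of CMS of 20" per cent, "an estimated frequency of a specific SNP of 30" per cent, and "a projected doubled risk of CMS with this particular SNP". From these the article concludes: "we will need to include a total of 343 patients to identify such a genetic predisposition at a 5% significance level with 90% power". It mentions no multiplicity, and neither this section nor Genetics names the SNP.

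The Genetics section describes a different kind of analysis. On the assay: "Genotyping will use single nucleotide polymorphism (SNP) exome enriched arrays (e.g. Illumina Omni2.5-exome platform"). On the analysis: "We will apply agnostic genome-wide association studies (GWAS) as well as more complex pathway analyses". The pathway work uses a neural-network method to test many pathways from several databases. Controls are to be drawn "using both non-CMS cases from the study cohort and non-CNS tumour patients as controls"; the number of the latter is not given. No genome-wide significance threshold appears.

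The genetic aim is among the items to be explored, listed after the primary and secondary endpoints. The target of 500 patients is given under Design.

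**The concern.** A power figure belongs to one test at one significance level. Here the level and the power are those of a single pre-specified comparison, while the analyses described search across an array and across pathways without a pre-specified SNP. Any threshold suited to such a search is far below 5%, and at that threshold the stated 90% is no longer available.

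At stake is how the genetic results will be read. Since 500 exceeds 343, a reader may conclude that the genetic question is comfortably powered. A GWAS with no hits could then be taken as evidence that no common variant doubles the risk, although the study would very probably miss such a variant.

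**Working it through.** **Inputs.** From Statistical considerations: overall CMS risk R = 20%, SNP frequency f = 30% (read as the share of carriers), relative risk 2, level 5% (taken as two-sided), power 90%, N = 343. From Design: N = 500. Assumed here: the thresholds 1e-5 and 5e-8. A second value of R follows from the surgical assumptions in the same section: 0.35 × 10% + 0.65 × 20% = 16.5%.

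**Risks by carrier status.** Non-carriers p0 = R / (0.7 + 0.3 × 2) = R / 1.3; carriers p1 = 2 × p0.
- R = 20%: p0 = 15.4%, p1 = 30.8%, difference 0.1538.
- R = 16.5%: p0 = 12.7%, p1 = 25.4%, difference 0.1269.

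**Reproducing 343.** With the overall variance in both terms, N = (1.960 + 1.282)² × 0.20 × 0.80 / (0.1538² × 0.30 × 0.70) = 338. A log-relative-risk formula gives 336 and a log-odds-ratio formula 350. All lie within 3% of 343.

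**Power formula.** Power = Φ[(p1 − p0 − z × SE0) / SE1], where SE0 = √[R(1−R)(1/n0 + 1/n1)], SE1 = √[p0(1−p0)/n0 + p1(1−p1)/n1], n1 = 0.3N and n0 = 0.7N.

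For R = 20% and N = 343 (102.9 carriers, 240.1 non-carriers), SE0 = 0.0471 and SE1 = 0.0511.
- At 5%, z = 1.960: (0.1538 − 1.960 × 0.0471) / 0.0511 = 1.20, so power is 88.5%, close to the stated 90%.
- At 5e-8, z = 5.451: (0.1538 − 5.451 × 0.0471) / 0.0511 = −2.02, so power is 2.2%.

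For R = 20% and N = 500, SE0 = 0.0390 and SE1 = 0.0423. At 5e-8: (0.1538 − 5.451 × 0.0390) / 0.0423 = −1.39, so power is 8.2%.

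**Same SNP at other levels** (range: R = 16.5% to R = 20%)

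| Two-sided level | N = 343 | N = 500 |
|---|---|---|
| 5% (one SNP) | 80–88.5% | 92–97% |
| 0.0025 (Bonferroni, 20 tests) | 46–59% | 67–80% |
| 0.0005 (Bonferroni, 100 tests) | 30–42% | 51–66% |
| 1e-5 | 8–14% | 20–33% |
| 5e-8 | 1.0–2.2% | 3.8–8.2% |

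By the same formula, 90% power at 5e-8 needs about 1,500 patients (R = 20%) to 1,900 (R = 16.5%). With 500 patients, the smallest relative risk detectable with 80% power at 5e-8 is about 3.0 (R = 20%) to 3.4 (R = 16.5%).

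**Extra controls.** At R = 20%, adding 500 to 5,000 non-CNS tumour controls with 30% carriers leaves power at 5e-8 at 1.0–1.3% (343) and 4.1–5.4% (500). The limit is the number of CMS cases: 0.20 × 343 ≈ 69, or 0.20 × 500 = 100.

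**Other readings of the inputs.** Two give more power at 5e-8, but neither leads to 343.
- Risks of 20% in non-carriers and 40% in carriers give 6.8% (343) and 23% (500). This needs only about 253 patients at 5% and 90%, and it contradicts the stated overall risk of 20%.
- Relative risk 2 per allele at 30% allele frequency gives about 21% and 55%. Power at 343 and 5% would then exceed 99%.

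**The case against.** The strongest reply is that the sentence claims no more than it should. It speaks of one particular SNP throughout and never says that the GWAS has 90% power. The genetic aim is introduced as exploratory, and the Genetics section itself expects the pathway approach to produce hypotheses for testing in other cohorts. The 343 sets nothing, because the target of 500 already exceeds the 450 given for the surgical question. A threshold and a multiplicity rule may well stand in an analysis plan that is not shown.

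Most of this stands, and it lowers the severity. It does not remove the mismatch: the only genetic power statement describes a test of an unnamed SNP, and whatever genome-wide threshold an analysis plan sets, the published 90% cannot carry over to the scan.

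A reader might also infer more than the article supports:
- That 343 is miscalculated. It is not; it reproduces for one SNP.
- That 5% would be applied to every SNP on the array, with a flood of false positives. Nothing says so.
- That the sizing SNP, which can account for only a small part of the variation, contradicts the statement "We hypothesize that host genome variants explain at least 50% of the variation in incidence of CMS". That statement concerns all variants together and is a hypothesis, not a success criterion. Nor does the article say that explained variation would be measured on the same data used to fit the model.
- That the low power holds for the whole genetic plan. The figures above do not describe the pathway or neural-network analyses; neither does 343.

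**Conclusion.** The point holds as a mismatch between the stated power and the analyses described, of moderate severity. For one pre-chosen SNP, 343 patients at 5% is about right at the stated 20% overall risk. For the agnostic GWAS, power for the same SNP is about 1–2% at 343 and 4–8% at 500.

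This rests on an assumed 5e-8 threshold, a two-sided test, 30% read as carrier share, and an overall risk between 16.5% and 20%. The conclusion does not depend on the exact threshold: at 1e-5, and even with correction for only 100 tests, power at 500 patients stays well short of 90%.

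**What to change.** 1. In Statistical considerations, limit the 343-patient, 5%, 90% statement to one candidate SNP, named before genotypes are linked to CMS. If a few candidates are wanted, give the Bonferroni-corrected level and restate the power; for 20 candidates it is about 67–80% at 500 patients.
2. State the GWAS threshold and its power at 500 patients. At 5e-8 this is about 4–8% for a relative risk of 2, and the smallest relative risk detectable with 80% power is about 3.0–3.4.
3. State that GWAS findings are hypothesis-generating, and that a null GWAS is not evidence against an effect of this size.

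The cost is a few sentences, with no extra patients or assays. The downside is a less favourable stated power.

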## Discussion

The study will be the largest prospective international study on CMS to date, and the first one to 1) systematically register surgery, use of steroids, standardized speech samples and 2) to investigate the influence of host genome. Detailed information on neuroradiological features, tumour and patient characteristics (incl. Handedness and pre-language impairment) will also be gathered, and may help further elucidate the incidence and clinical course of the syndrome for various patient and tumour types.

On-line registration compliance rates to Nordic/Baltic multicentre trials are in general above 95% [62]. Furthermore, we will implement an automated email reminder system at the four follow-up time points and the project coordinator and data manager will validate all data inputs, request clarifications and updates for unclear or missing data, and secure that DNA of sufficient quality is received, processed and stored for later host genome analyses.

Currently, a randomized intervention study is unrealistic due to limited data supporting any specific neurosurgical approach and given the diversity of tumour subtypes, localisation and invasiveness. However, such a randomisation may be realistic if the present study does not clearly identify surgical approaches with statistically significant reduced risks of CMS.

## Abbreviations

CMS: Cerebellar mutism syndrome
CNS: Central nervous system
GWAS: Genome-wide association studies (GWAS)
SNP: Single nucleotide polymorphism
